## 8. STUDY INTERVENTION

### 8.1 Investigational Products (treatment / medical device)

Schülke & Mayr GmbH will provide 550 octenisan® sets free of charge for use during the BALGDEC trial. The sets will be used according to the instruction provided in the patient information leaflet. The instructions will be available in German, English, French and Italian languages.

The active ingredient contained in octenisan® set (octenisan® wash lotion and octenisan® md nasal gel,  no. article 11636528, EAN 4032651979264) is octenidine dihydrochloride. One set costs on the Swiss market approximatively 22,25 CHF.-

The wash lotion is applied once a day. The nasal gel is applied 2-3 times per day.

#### 8.1.1 Intervention treatment

The duration of pre-surgical decolonization is planned to be five days. However, when this pre-surgical time period is too short, the decolonization may also start at least 3 days before surgery and may be continued up to 2 days post-surgery. In case of post-surgery application, the patient will be washed with water and octenisan® wash lotion by their treating nurses. The patient will also return the empty/used set and answer to a short questionnaire during their hospital stay. The study team will recuperate the questionnaire during hospitalization.

During decolonization, patients are asked to change the bed linen and underwear every day and not to share towels, clothes and other textiles with their family or pets. They may use their habitual perfumes, but must not use other antiseptic agents, body lotions or moisturizer during the decolonization period.

#### 8.1.2 Control Comparator

Absence of decolonization and absence of the questionnaire.

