| Questionnaire                            |                         |                            | X                                                | X                        |                                            |
| Compliance                               |                         |                            | X                                                | X                        | X                                          |
| Adverse Events                           |                         | X                          | X                                                | X                        | X                                          |
| Study End                                |                         |                            |                                                  | X                        | X                                          |

We assess:

Patient's characteristics (age, sex, body mass index, renal insufficiency, cirrhosis, other immune-suppressions, diabetes, pregnancy), indication of surgery, presence of osteosynthesis, all postoperative complications, surgical site infections and pathogens, all adverse events during hospitalization, length of hospital stay, duration of an eventual VAC (vacuum-assisted closure) / PICO use, and the patient's opinion on the use of the decolonization set (patient questionnaire) immediately after surgery.

The previously validated questionnaire will be in German language with five open questions: Practical difficulties of decolonization, the completeness of scheduled decolonization actions, all adverse events during decolonization and surgery, and two questions regarding the comprehension of the science (indication for decolonization, potential benefit expected in the individual case).

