### Secondary outcomes:

- Unplanned revision surgery for non-infection problems in same time period
- All adverse events during decolonization and hospitalization for surgery
- Subjective opinion on the decolonization (only for patients being decolonized)

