#### 9.1.2 Assessment of other outcomes of interest

Secondary objectives are adverse events, unplanned revision surgery for non-infection problems in same time period, and the subjective opinion on the decolonization (only for patients being decolonized). We will note them during the study visits and per questionnaires (for the patients participating in the decolonization).

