#### **9.2 Procedures at each visit for both prospective-randomized studies**

At enrollment (Visit 1 / Day 1), patients will be randomized at ratio 1:1 into the investigational group (decolonization) and the control group (no decolonization). The study investigators will instruct the correct decolonization procedure. During the decolonization period, patients can also review the patient information leaflet of the set for details on the decolonization procedure. The questionnaire will be handed over to the decolonization patients.

The treatment period includes the following study visits:

- Visit 1 - Enrollment (Day 1)
- Visit 2 - End-of-Treatment (EOT) -Visit is the Day of Surgery or Day 1-2 after surgery
- Visit 3 - Test-of-Cure-Visit (TOC) (clinical surgical control) - Day 42 (+/- 14 days)
- Follow-up (eventually by phone call) for implant-related surgery after 1 year (+/- 2 months).

During the study visits, we assess the history, wounds, adverse events, and the functional status. We examine the patients according to the orthopedic standard, and add supplementary laboratory exams and radiology, only if clinically indicated.

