##### 10.1.2 Definition and assessment of (serious) adverse events and other safety related events

###### *Adverse event*

An **Adverse Event (AE)** is any untoward medical occurrence in a patient or a clinical investigation participant administered the investigational product and which does not necessarily have a causal relationship with the investigational product. An AE can therefore be any unfavourable and unintended sign (including an abnormal laboratory finding), symptom, or disease temporally associated with the use of the investigational product, whether or not related to the investigational product.

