#### 11.3.1 Interim analysis and early termination

We will perform one interim analysis one year (+/- 2 months) after the inclusion of the first patient. If group comparison between the decolonization and non-decolonization arms are striking and statistically significant in terms of any study objectives, the independent Data Monitoring committee will decide upon the interruption and early termination of the trial. Otherwise, the study continues. Of note, the Data Monitoring committee has the right to call on a premature, additional interim analysis.

If the crude group comparison analysis is not sufficiently meaningful, we will perform a futility analysis to check if the expected statistical power for the final analysis will not be  $< 30\%$  and therefore unacceptable. If it is lower than  $30\%$ , we will consider the trial will not be able to demonstrate the result, and the recruitment will be no more ethical. The most frequent conditional power evaluated under the current trend (i.e. using the information from the collected data) will be assessed. It was demonstrated that futility analyses decrease the statistical power of the final analysis in superiority trials, but in our knowledge, this topic was not explored for non-inferiority trials. To balance (at least partially) this loss of power, we may recruit 100 supplementary patients per arm. E.g. approximately 600 episodes in each randomization arm.

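### Non-serious adverse events are collected from an extra source and over extra days in the decolonization arm only, so the between-arm safety comparison leans against decolonization

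*Protocol*

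**What the plan says.** - **Source.** The questionnaire described under the Study Schedule has five open questions, one of them covering "all adverse events during decolonization and surgery, and two questions regarding the comprehension of the science". Section 9.2 states that "The questionnaire will be handed over to the decolonization patients", and Section 8.1.2 defines the control arm as "Absence of decolonization and absence of the questionnaire". On the secondary outcomes, AEs among them, Section 9.1.2 says: "We will note them during the study visits and per questionnaires (for the patients participating in the decolonization".
- **Window.** Section 5 lists as a secondary outcome "All adverse events during decolonization and hospitalization for surgery". Section 8.1.1 plans five days of decolonization before surgery, or a start at least three days before with continuation up to two days after.
- **Definition.** Section 10.1.2 describes an AE as "any untoward medical occurrence in a patient or a clinical investigation participant administered the investigational product", associated in time with use of that product.
- **What both arms share.** The Study Schedule marks AEs at Visits 1, 2 and 3 and at the one-year follow-up without restriction by arm. Section 9.2 assesses AEs at the study visits, Sections 9.2.3 and 9.2.4 take a history of past AEs, and Section 10.1 collects serious AEs from the signing of consent.
- **Use of the comparison.** Section 4 makes safety an objective. Section 11.3.1 lets the committee decide on early termination if the arms differ in a way that is "striking and statistically significant in terms of any study objectives".

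**The concern.** A comparison of AE frequency between arms is interpretable only if events are sought in the same way and over the same time in both. Here the decolonization arm has visits plus a questionnaire, and controls have visits only. The questionnaire item also covers the surgical period, which both arms go through, so the additional capture is not confined to reactions to the product. The decolonization arm further contributes pre-operative days that are not defined for controls. Both features add recorded events on one side.

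The events most affected are those of most interest for this product: Section 3.6 names skin irritation, intolerance and allergy as the possible harms of decolonization. A product with no effect on AEs could thus appear less well tolerated, and the committee could be shown that difference at the interim.

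**Working it through.** **Sources side by side**

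| | Decolonization | Control | Place |
|---|---|---|---|
| AEs at study visits | yes | yes | Study Schedule; 9.2 |
| Serious AEs from consent | yes | yes | 10.1 |
| Questionnaire with an AE item | yes | no | Study Schedule; 8.1.2; 9.1.2; 9.2 |
| Decolonization days in the AE outcome | yes | no matching period defined | 5; 8.1.1 |
| Literal fit of the AE definition | yes | no | 10.1.2 |

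The last three rows differ, and all in the same direction.

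**The plan's own figure.** The protocol gives no AE rate and sets no sample size for AEs. Its only nearby figure is the primary sample size, 10% versus 5% with 80% power at two-sided 0.05:

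n = [1.96·√(2·0.075·0.925) + 0.8416·√(0.10·0.90 + 0.05·0.95)]² / 0.05² = 434.4, so 435 per arm.

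With continuity correction, (434.4/4)·[1 + √(1 + 4/(434.4·0.05))]² = 473.6, so 474. The stated 474 reproduces and is not in dispute.

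**Illustration of size (assumed rates).** Let p0 be the recorded AE proportion in controls and p1 = p0 + e, where e comes from extra capture alone and the true risk is equal in both arms. With p̄ the mean of p0 and p1:

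- SE0 = √[2·p̄(1−p̄)/n]
- SE1 = √{[p1(1−p1) + p0(1−p0)]/n}
- P(p≤0.05) = 1 − Φ[(1.96·SE0 − e)/SE1] + Φ[(−1.96·SE0 − e)/SE1]

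Example with p0 = 0.10, e = 0.02, n = 500: p̄ = 0.11, SE0 = 0.01979, SE1 = 0.01978. The upper argument is (0.03879 − 0.02)/0.01978 = 0.950, giving 0.171. The lower tail adds 0.0015. The total is 17.3%.

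The final size is 500 per arm (Section 11.2). For the interim at one year I take half of that, 250 per arm; the synopsis estimate of 600 eligible episodes per year would give up to 300.

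| Extra points e | p0 = 10%, n = 500 | p0 = 10%, n = 250 | p0 = 30%, n = 500 | p0 = 30%, n = 250 |
|---|---|---|---|---|
| 0 | 5.0% | 5.0% | 5.0% | 5.0% |
| 1 | 8.1% | 6.5% | 6.4% | 5.7% |
| 2 | 17.3% | 11.0% | 10.5% | 7.7% |
| 4 | 49.5% | 28.0% | 27.3% | 16.0% |
| 5 | 66.7% | 39.4% | 39.3% | 22.2% |

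**The window alone.** If the in-hospital risk is 10% in both arms and the pre-operative days carry a background risk r counted on one side only, p1 = 1 − 0.90·(1 − r). For r = 1%, 2% and 5% this is 10.9%, 11.8% and 14.5%, that is 0.9, 1.8 and 4.5 extra points. At 250 per arm the chance of a significant excess against decolonization is 5.1%, 9.4% and 33.5%, where 2.5% is nominal for that one direction.

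**The case against.** **The visits may already capture these events.** AEs are assessed at every visit in both arms, and Visit 3 and the one-year follow-up take a history of past events. Much of what the questionnaire elicits could surface there, and its extra yield may be small. This stands as a limit on size. It does not remove the imbalance, because the additional source and days lie on one side only.

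**The questionnaire is mainly about experience and compliance.** Withholding it from controls is defensible for the handling, completeness and comprehension items. That is right; only the AE item is at issue.

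**AEs are largely descriptive.** No AE hypothesis is stated. However, Section 11.3 plans group comparisons and Section 11.3.1 refers to any study objective, so a between-arm AE test is within the plan.

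**Stronger readings.** A reader might infer that the arms have two different AE definitions, or that control AEs go unrecorded. The protocol has one definition, worded for exposed participants and a poor fit for controls, and its visit schedule has AEs recorded in both arms. A reader might also infer that the artefact would stop the trial. Section 11.3.1 requires a difference that is striking as well as significant, followed by a committee decision; nothing is automatic.

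**Conclusion.** The point holds as an ascertainment imbalance for non-serious AEs. Serious AEs from consent, visit-based AEs, the primary outcome and its sample size are not affected. The direction is clear from the text. The size cannot be computed from the documents: every AE rate above is assumed, episodes are treated as independent, and the chance of a spurious finding runs from the nominal 5% with no extra capture to about 67% with five extra points on a 10% base at 500 per arm. A higher base rate gives less inflation. None of these values should be read as an estimate for this trial.

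At the interim, a biased AE comparison could inform the stopping decision without determining it. A later analysis plan could restrict the comparison to shared sources, but it could not recover answers to a question that controls were never asked. The change should therefore be made in the protocol.

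**What to change.** 1. In Section 10.1.2, define an AE for every randomised participant, irrespective of exposure to the product.
2. In Sections 4 and 5, replace the decolonization-based period by one window for both arms, from randomisation to discharge (and to Visit 3).
3. In Section 9.1.2, base any between-arm AE comparison, including at the interim, only on AEs recorded at the common visits. Report the questionnaire AEs of the decolonization arm separately and descriptively. Alternatively, put the same single AE question to controls at Visit 2 and leave the other questionnaire items in the decolonization arm.

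The cost is protocol wording. With the first option in step 3, some patient-reported AEs leave the comparison. With the second, one question is added at an existing visit for about 500 control episodes. Because the trial is unblinded, patients and assessors may still report differently by arm at the common visits; that residual bias should be acknowledged.

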#### 8.1.3 Storage Conditions

The sets can be stored at ambient temperature for several months, as indicated on the packaging of both investigational products. They will be in the (locked) office of the Infection Control nurses and in the [name] office.

### 8.2 Dose modifications

n.a.

### 8.3 Compliance with study intervention

We assess the auto-declared compliance of the patients in the intervention (decolonization) arm via questionnaires and by recuperating the empty packages of the decolonization sets.

#### 8.4 Data Collection and Follow-up for withdrawn participants

Withdrawn participants are instructed to continue surveillance according to the protocol and to contact the investigators if there are any questions or concerns that arise after completing the study.

#### 8.5 Trial specific preventive measures

n.a.

#### 8.6 Concomitant Interventions (treatments)

Standard wound control for all patients will include eventual wound debridement (during hospitalization or at clinic visits and only if clinically indicated), regular wound care with dressing changes and eventual VAC use in selected cases upon surgical indication. We will avoid topical antibiotics.

#### 8.7 Accountability of the investigational product

We recuperate the packages of the used decolonization sets from the patients during hospitalization and/or shortly after surgery and this process will be documented (e.g. accountability log). This log should also serve to record any damages of the set.

#### 8.9 Return or Destruction of Investigational Product

Returned used and unused decolonization sets will be destroyed at the end of the investigation, as the sets will be provided for the purpose of this clinical investigation only. The patient will also have be informed about the return of the investigational product. This notice will be captured in the participant information sheet or in the informed consent.

### 9. STUDY ASSESSMENTS

#### 9.1 Assessment of primary outcome

Judged by local wound healing (healed vs delayed wound healing according to Reference). The wound healing will be assessed visually by orthopaedic surgeons. Wound nurses and the study investigators may help in the assessment of wound problems, but in case of doubtful cases, the opinion of the treating physician will dominate the decision upon the presence or absence of wound problems and/or infection.

Persistent postsurgical pain, serum laboratory markers, or the patient's subjective wound feelings will not serve as objective criteria for wound healing (or in the contrary, wound discharge and dehiscence). A wound problem solely due to stitches and localized suture problems will not count as a wound problem. A keloid or altered pigment features will not be counted as a problem in this trial. Remission is defined as the absence of any problems and as the absence of any clinical signs of infection.

The primary outcome will be assessed on both, the Intention-to-treat and the per-protocol populations.

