The duration of pre-surgical decolonization is planned to be five days. However, when this pre-surgical time period is too short, the decolonization may also start at least 3 days before surgery and be continued up to 2 days post-surgery. During the post-surgery application, the patient will be washed with water and octenisan® by their treating nurses. The patient will also return the empty/used set and answer to a short questionnaire during their hospital stay. The study team will recuperate the questionnaire during hospitalization. We renounce on routine microbiological assessments of skin colonization, but the hospital's infection control can demand it for other reasons regarding infection control. Hence, skin colonization data will only be available for some selected patients that are screened for body carriage of antibiotic-resistant pathogens, according to the infection control recommendations in Switzerland.

There will be a Monitoring at study start, the interim analysis and at the end.

The primary study outcomes are unplanned revision surgery for SSI and wound problems at 42 days for all surgeries; or 1 year in case of an implant-related surgery. Secondary objectives are other unplanned revision surgeries for non-SSI reasons, all adverse events, as well as patient's subjective impression of the decolonization.

The treatment period includes the following daily study visits:

- Visit 1 - Enrollment (Day 1)
- End-of-Treatment (EOT) -Visit is the Day of Surgery or Day 1-2 after surgery
- Test-of-Cure-Visit (TOC) (clinical surgical control) - Day 42 (+/- 14 days)
- Further follow-up (eventually by phone call) for implant-related surgery - 1 year (+/- 2 months)

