## Outcome(s)

### Primary outcomes

- Remission (and inversely superficial or deep-space SSI and revision surgeries for non-infected wound problems; composite primary outcome) at 6 weeks (and/or a 1 year for surgeries with implant)

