#### 3.2.1 Study definitions

An orthopedic infection for this trial is the microbiological evidence of bacteria in at least two intraoperative tissue samples together with radiological (osteomyelitis, collections, inflammation) and/or clinical evidence of infection (pus, discharge, sinus tracts, rubor, calor, pain). Histological proof is facultative for this study. Implants are defined as any implants except for transient wires or fixator pins. A wound problem is any unplanned post-surgical wound pathology leading to surgical revision. Remission of infection is the absence of clinical and/or radiological and/or laboratory signs of (former) infection after the minimal follow-up time of 1 year for implant -related surgery with implants left in place; or two months for implant-free surgery (including surgery when all implants have been removed)..

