## 5. STUDY OUTCOMES

### Primary outcomes:

- Remission (and inversely superficial or deep-space SSI and revision surgeries for non-infected wound problems; composite primary outcome) at 6 weeks (and/or a 1 year for surgeries with implant)

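### Sections 5 and 9.1 code the same wound differently: a non-infected wound that heals late without surgical revision is no primary event in one and not in remission in the other

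*Protocol*

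**What the plan says.** Three places tie the non-infected part of the primary outcome to an operation:

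- Section 3.2.1: "A wound problem is any unplanned post-surgical wound pathology leading to surgical revision".
- Section 5, repeated in the synopsis outcome list: "Remission (and inversely superficial or deep-space SSI and revision surgeries for non-infected wound problems; composite primary outcome) at 6 weeks", extended to one year for implant surgery.
- Synopsis, Study Conduct: "The primary study outcomes are unplanned revision surgery for SSI and wound problems at 42 days for all surgeries".

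Section 9.1, on how the primary outcome is assessed, uses other terms. It begins "Judged by local wound healing (healed vs delayed wound healing according to" Reference 4, which section 16 lists as the WHO guideline on preventing surgical site infection. The wound is assessed visually by orthopaedic surgeons. Discharge and dehiscence are mentioned as the contrary of healing. Suture problems, keloid and pigment changes are excluded. Then: "Remission is defined as the absence of any problems and as the absence of any clinical signs of infection". In doubtful cases "the opinion of the treating physician will dominate the decision upon the presence or absence of wound problems and/or infection".

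Section 8.6 foresees wound care short of revision for all patients: "eventual wound debridement (during hospitalization or at clinic visits and only if clinically indicated), regular wound care with dressing changes and eventual VAC use", the last of these for a subset only.

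**The concern.** One endpoint appears to have two rules. Wounds that heal slowly or open up and are managed conservatively lie between them: the protocol expects to treat such wounds (8.6), does not exclude them in 9.1, and does not count them in section 5. An assessor following section 5 codes such a patient as event-free. An assessor following 9.1 codes the same patient as not in remission.

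This is more than a detail that a statistical analysis plan could settle later. Wounds are classified at the visits, from the protocol. The trial is unblinded and the treating physician decides doubtful cases, so an unclear rule leaves room for inconsistent coding. The planned event rates were also set for only one of the two rules.

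**Working it through.** **1. Test case.** Take a patient with a non-infected wound and delayed healing or dehiscence, managed with dressings, VAC or debridement at a clinic visit. Nobody would call the wound surgically revised.

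| Place in the protocol | What it counts for a non-infected wound | Code for the test case |
|---|---|---|
| 3.2.1 | pathology leading to surgical revision | no wound problem |
| Section 5 and synopsis outcome list | revision surgery | no event |
| Synopsis, Study Conduct | unplanned revision surgery | no event |
| 9.1, opening criterion | healed or delayed healing, per Reference 4 | delayed |
| 9.1, remission | no problems and no clinical signs of infection | not in remission |

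**2. Complement check.** Section 5 presents remission and the composite as inverses. No composite event therefore means remission. By section 5 the test case is in remission; by 9.1 it is not. Both cannot hold, and no section states an order of precedence.

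**3. Which rule the sizing follows.** Section 11.2 sets 10% for revision surgery and/or SSI, against 5% with decolonization, with 80% power. Section 11.3 gives two-sided 0.05. With p1 = 0.10, p2 = 0.05 and mean 0.075:

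n = [1.960 × √(2 × 0.075 × 0.925) + 0.842 × √(0.10 × 0.90 + 0.05 × 0.95)]² / 0.05² = (0.7301 + 0.3121)² / 0.0025 = 434.4

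With continuity correction: (434.4 / 4) × [1 + √(1 + 4 / (434.4 × 0.05))]² = 473.6, so 474 per arm.

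The stated 2 x 474 reproduces. The figure is not in dispute. It rests on the section 5 type of event, not on delayed healing.

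**4. Why no effect size follows.** The documents give no rate for non-revised wound problems. Suppose counting them adds x to the control rate. Power at 500 per arm, without continuity correction, would then be:

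| Assumed x | Same x added in both arms | Decolonization halves x |
|---|---|---|
| 0 | 85% | 85% |
| 2% | 77% | 91% |
| 5% | 67% | 97% |
| 10% | 55% | 99% |

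For example, x = 2% compares 12% with 7% in the first column and 12% with 6% in the second. Power can fall or rise according to an assumption that the documents do not settle.

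**The case against.** The strongest defence is to harmonise the texts. Section 3.2.1 gives a trial-wide definition of a wound problem, and 9.1 uses that term repeatedly. The sentence on remission comes directly after two sentences on what does not count as a problem. Read with the defined term, remission would mean no revised wound problem and no sign of infection, which is the section 5 inverse. One can add that section 5 defines the outcome while 9.1 only describes its assessment.

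Part of this stands. The word 'problems' in 9.1 can be read that way. The exclusions of suture problems and keloid do not disprove it, since those too can be revised and would otherwise count under 3.2.1. The defence does not, however, dispose of the opening criterion. A contrast between healed and delayed healing, judged visually and with dehiscence as its contrary, is hard to confine to revised wounds. Section 9.1 also contains a definition of its own, so it does more than describe assessment.

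A second objection is that delayed healing is tied to Reference 4, which cannot be consulted here. If that source restricted the term to wounds needing revision, the conflict would shrink. This is why the point is put as the natural reading of 9.1 and no further.

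A third objection is that discretion survives any rewording: the decision to reoperate is also made by clinicians in an unblinded trial. That is correct. The fix removes the contradiction in wording, not the scope for unequal ascertainment.

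**Conclusion.** The contradiction stands for one class of patients: non-infected wounds with delayed healing or dehiscence that are managed without surgical revision. They are non-events by 3.2.1, section 5 and the synopsis and, on the natural reading of 9.1, not in remission. The wording of the primary outcome should be corrected.

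The conclusion rests on reading delayed healing in its ordinary sense, because Reference 4 cannot be checked, and on there being no statement of which section prevails. Its size is unknown, as the documents give no frequency for these wounds.

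A reader might infer three stronger things, none of which the documents support:

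- **The trial is underpowered.** Even the sign of any change in power depends on assumed rates and effects.
- **The result will be biased in a known direction.** An unblinded assessor and an unclear rule make unequal coding possible. Nothing shows that it will occur or which arm it would favour.
- **The treatment of an SSI that is never operated on is settled by the same correction.** That is a separate matter: the infection definition in 3.2.1 asks for bacteria in two intraoperative tissue samples, and aligning 9.1 does not change it.

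**What to change.** In 9.1, replace the healed-or-delayed criterion and the remission sentence with the section 5 composite: remission is the absence of SSI and of unplanned surgical revision for a non-infected wound problem as defined in 3.2.1. Apply the treating physician's ruling in doubtful cases to that event. Add one sentence stating that delayed healing, debridement or VAC without surgical revision is not a primary event.

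The cost is a wording change in 9.1. Section 5, the 11.2 sample size and the planned tests stay as they are, and the assessed event then matches the one used for sizing. The downside is that wounds managed without revision leave the primary outcome. A sensitivity analysis that also counts them would keep that information.
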